**ENROLMENT**							
**Eligibility screen**	X						
**Informed consent**	X						
**Allocation**		X					
**INTERVENTIONS**							
***Esketamine infusion***				X			

### Interventions

The esketamine treatment protocol differs for the continuous inpatient and intermittent outpatient treatment arms. The inpatient protocol is derived from a study by Sigtermans et al. [22]. For the inpatient treatment arm, esketamine is administered intravenously in CRPS patients for 6 consecutive days. Esketamine dose will be started at 0.05 mg/kg/h and can be increased to a maximum of 0.2 mg/kg/h. The dose can be increased with steps of 0.05 mg/kg/h every hour. For the outpatient treatment arm, esketamine will be administered for 6 hours. Esketamine dose will be started at 0.05 mg/kg/h and can be increased to a maximum of 0.2 mg/kg/h. The dose can be increased with steps of 0.05 mg/kg/h every hour. The increase of the esketamine dose depends on whether the patient experiences pain reduction or side effects. Once the patient notices a reduction in pain, the esketamine dose is not increased further for the duration of their admission. The investigators consider this the effective dose. If the effective dose in an earlier treatment session was higher than 0.05 mg/kg/h, the effective dose can be used as the starting dose in the following outpatient treatments.

If the patient experiences debilitating side effects the dose is reduced until the side effects disappear. Psychomimetic effects of esketamine will be treated with intravenous benzodiazepines or clonidine if necessary. In case of nausea and/or vomiting, intravenous granisetron will be administered. If the side effects subside, the esketamine dose is increased again and effects and side effects are closely monitored. If debilitating side effects persist, the esketamine therapy is discontinued. Side effects, vital parameters and pain scores will be frequently monitored by a nurse. As esketamine can induce hepatotoxicity, liver enzymes are monitored before administration and at the third day of the inpatient treatment or at the third outpatient esketamine treatment (aspartate aminotransferase (AST), alanine aminotransferase (ALT), lactate dehydrogenase (LDH), alkaline phosphatase (AF) and gamma-glutamyl transferase (GGT) [23].

### Outcomes

The primary outcome parameter is perceived pain intensity measured by Numerical Rating Scale (NRS) at T3 and will be compared to the baseline NRS pain scores (T0). The NRS ranges from 0 (no pain) to 10 (worst pain imaginable). Both the current NRS pain score and the average NRS pain score of the last 24 hours will be asked during all study visits.

Several secondary outcome parameters will be assessed. First, sensory-discriminative dimensions of pain are assessed by using quantitative sensory testing (QST) (T0, T3) [24]. QST is a standard set of tests to characterize how somatosensory stimuli are processed and is also used to examine which types of nerve fibers might be damaged [24]. Second, information on the endogenous pain inhibitory pathway of CRPS patients will be assessed with conditioned pain modulation (T0, T3) [25]. Third, inflammatory activity will be assessed by measuring the serum level of soluble IL-2 receptor (sIL-2R) (T0, T3). sIL-2R is a surrogate marker for T-cell activation and may be used as a biomarker for monitoring T-cell involvement in CRPS-related inflammation [26, 27]. Fourth, temperature asymmetry will be measured by thermographic imaging at T0 and T3. Thermographic imaging was previously shown to be a reliable additive diagnostic tool to determine temperature differences between the affected and contralateral extremity in CRPS patients [28]. Fifth, pain intensity, syndrome severity, participation and function, emotional and physiological function, self-efficacy, catastrophizing and patient global perceived effect are assessed using the questionnaires of the core outcome measurement set for complex regional pain syndrome clinical studies (COMPACT) (T0, T2, T3, T4) [19]. The COMPACT questionnaires are defined by an international consortium of patients, clinicians and researchers as minimum core set of standardized, patient-reported questionnaires that cover important domains about the presentation and course of CRPS and factors that influence the syndrome (see Table 2) [19]. Sixth, the (effective) esketamine dose during infusion (T1). Seventh, adverse events related to esketamine treatment: dysphoria, euphoria, hallucinations, nightmares and vivid dreams, anxiety, agitation, blurry vision or diplopia, nausea or vomiting, sedation, hepatic toxicity, headache, phlebitis, infiltration/extravasation and dislodgement of peripheral intravenous catheter (T1, T2). Eight, number of administered co-interventions (benzodiazepines, clonidine, granisetron) related to adverse events (T1). Ninth, changes in the dose of pain medication during study enrolment (T0, T3, T4). Tenth, resource use and costs per patient will be assessed. Eleventh, changes in participation in employment, education or voluntary work during study enrolment (T0, T3, T4). Last, the difference in NRS pain scores over time at T1, T2, T3 and T4. The results of baseline tests or parameters will serve as a baseline and all subsequent evaluations will be compared with these results.

**Table 2 Tab2:** Questionnaires used in KetCRPS-2 study. *Adapted from the Core Outcome Measurement set for complex regional PAin syndrome Clinical sTudies (COMPACT)* [19]

COMPACT questionnaires [19]	Details	Study period assessed
Global Perceived Effect (GPE) [20]	The Global Perceived Effect asks the patient to rate, on a numerical scale, how much their condition has improved or deteriorated since some predefined time point.	T2, T3, T4
PROMIS-29 Profile version 2.1 [29]	Assesses 7 domains, each with 4 questions: depression, anxiety, physical function, pain interference, fatigue, sleep disturbance, and ability to participate in social roles and activities.	T0, T3
Short-form McGill Pain Questionnaire-2 (SF-MPQ-2) [30]	Six neuropathic items capturing the quality of pain	T0, T3
Pain Catastrophizing Scale [31]	To measure how catastrophizing affects the pain experience.	T0, T3
EQ-5D-5L [21]	To measure health state, comprising mobility, self-care, usual activities, pain/discomfort, anxiety/depression	T0, T3, T4
Pain Self-Efficacy Questionnaire [32]	The respondent considers how confident they are performing each activity, while taking their pain into account	T0, T3
CRPS severity score [14]	CRPS symptoms and signs based on the Budapest diagnostic clinical criteria	T0, T3

### Baseline measurement T0

The patients are invited to the Center for Pain Medicine for a baseline measurement. Information on demographics, CRPS-affected limb(s), CRPS duration and medication is obtained during history taking. The patients will be asked for NRS pain scores. During the baseline visit, the CRPS severity score will be assessed [14]. At both T0 and T3, peripheral blood samples will be taken to obtain information on the serum sIL-2R level and the total set of the COMPACT questionnaires will be completed [19].

QST at the Center for Pain Medicine is measured according to the protocol by Rolke et al. and provides diagnostic information on the somatosensory profile of the CRPS affected area [24]. At T0, the entire QST protocol by Rolke et al. is conducted to give information on the baseline somatosensory profile of the included patients. In addition, the protocol by Rolke et al. [24] may be used in CRPS as a diagnostic test for phenotyping different CRPS subgroups. QST consists of thermal, pressure, mechanical sensation and pain thresholds and these stimuli are measured using thermodes, pinpricks, Von Frey filaments, electrical stimulation and an algometer. All tests will first be performed on the clinically unaffected contralateral side before testing on the CRPS-affected side. The punctum maximum of pain on the CRPS-affected side was used as the reference for the anatomical testing location and will also be used on the clinically unaffected contralateral side.

The conditioned pain modulation protocol used in this RCT is based on the protocol used at the pain department of Radboud University Nijmegen, the Netherlands [33, 34] and adapted from Kriek et al. [35] at our department. All conditioned pain modulation tests are done in a standardized order. We use electrical stimulation and pressure algometry for the test stimuli. For electrical stimulation, the current perception threshold (CPT) and pain perception threshold (PPT) are determined three times with an ascending electrical stimulation protocol at the upper extremity at the contralateral side of the affected CRPS extremity. The conditioned pain modulation protocol is enriched with an additional test stimulus according to Yarnitsky et al. [36] by using pressure algometry. For pressure algometry, the current perception threshold (CPT) and pain perception threshold (PPT) are determined three times with an ascending pressure algometry protocol at the trapezius muscle. The ipsilateral healthy extremity of the CRPS affected extremity is submerged in ice water as the conditioning stimulus. For the full conditioned pain modulation protocol see Additional file 1. Our conditioned pain modulation analysis method is adapted from Olesen et al. [37] and Kriek et al. [35]. The PPTs will be determined three times, and the median value of these three values will be calculated for further analysis. By taking medians, outliers will not be taken into analysis. Ratios will be used to investigate the relationship of the threshold between the affected CRPS side and the healthy contralateral side [35, 37]. The advantage of using ratios is that they eliminate the intersubject differences in absolute CPT and PPT [35]. The ratio of each PPT threshold is calculated by using the formula (threshold CRPS affected side) / (threshold healthy contralateral side) [35]. This yields the CPT ratio and PPT ratio of the electrical stimulation and pressure algometry.

At the Center for Pain Medicine, a thermal imaging camera is used in standard clinical practice to measure skin temperature and detect temperature asymmetry in CRPS patients. In this study, thermography will be conducted to detect temperature differences that may be caused by esketamine treatment. Specialized researchers use a camera from FLIR Advanced Thermal Solutions to detect temperature asymmetry (FLIR T1020).

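### The conditioned pain modulation index stated in the protocol is an affected/contralateral ratio: it measures side asymmetry and contains no contrast between thresholds without and with ice water

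*Protocol article*

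**What the plan says.** All references are to the protocol article.

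- **Outcomes** gives the purpose: "information on the endogenous pain inhibitory pathway of CRPS patients will be assessed with conditioned pain modulation (T0, T3").
- **Baseline measurement T0** describes the test. On the stimuli: "We use electrical stimulation and pressure algometry for the test stimuli". Electrical thresholds "are determined three times with an ascending electrical stimulation protocol at the upper extremity at the contralateral side of the affected CRPS extremity". Pressure thresholds "are determined three times with an ascending pressure algometry protocol at the trapezius muscle"; which side is not given. On conditioning: "The ipsilateral healthy extremity of the CRPS affected extremity is submerged in ice water as the conditioning stimulus".
- The same section then sets out what it calls its analysis method for conditioned pain modulation. The median of three pain thresholds is taken, and ratios are used to relate the affected side to the healthy side: "The ratio of each PPT threshold is calculated by using the formula (threshold CRPS affected side) / (threshold healthy contralateral side"). The stated output is one perception-threshold ratio and one pain-threshold ratio for each of the two stimuli.
- The full test procedure is referred to Additional file 1, which is not shown.
- **Follow-up measurement T3** keeps conditioned pain modulation in the shortened test set because it might predict pain relief. The **Discussion** counts it among the measures hoped to separate responders from non-responders.

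**The concern.** Conditioned pain modulation is the change in a test threshold when a second painful stimulus, here ice water, is applied. An index of it needs two conditions: the threshold without the ice water and the threshold during or after it. The stated formula has two sides of the body instead, and no term for condition.

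The formula also does not match the test described just before it. It needs an affected-side threshold, while the electrical test is placed on the contralateral upper extremity only.

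At stake is what a result on this outcome would mean. With the stated index, no difference between arms or between T0 and T3 would not show that pain inhibition was unchanged, and a difference could reflect altered side asymmetry. Either could be reported as a finding about inhibition, and either could enter the search for predictors of response.

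**Working it through.** The documents give no sample size, power or effect size for this outcome, so there is no figure to reproduce. The check sets the test against the formula and then examines how the formula behaves.

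**1. Can the described test fill the formula?**

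| Stimulus | Site described | Contralateral threshold (denominator) | Affected-side threshold (numerator) |
|---|---|---|---|
| Electrical | Upper extremity, contralateral to the CRPS limb | Yes | Not produced |
| Pressure | Trapezius, side not stated | Unclear | Unclear |

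For electrical stimulation the conflict is explicit. For pressure the text is only incomplete: testing on both sides is neither stated nor excluded.

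**2. Could QST supply the missing side?** Under Baseline measurement T0, QST is done on both sides and includes electrical stimulation and an algometer, so affected-side thresholds may exist at T0. But QST is listed as a separate outcome, the text does not link it to this ratio, and the T3 section repeats only conditioned pain modulation, pressure algometry and temporal summation. QST electrical thresholds are not in that T3 set. A ratio of QST thresholds would in any case involve no ice water.

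**3. Does the formula respond to conditioning?** Let A and C be the affected and contralateral thresholds without ice water, and let conditioning multiply them by kA and kC.

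- Taken without ice water, the ratio is A/C and contains no conditioning.
- Taken with ice water, it is (kA × A)/(kC × C) = (A/C) × (kA/kC).
- If kA = kC, the factor cancels and the ratio is again A/C.

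Illustration with assumed thresholds (the documents give none), A = 6 and C = 10, and a common factor k:

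| k | Side ratio with ice water | With/before ratio at the contralateral site |
|---|---|---|
| 0.8 | 4.8/8 = 0.60 | 8/10 = 0.8 |
| 1.0 | 6/10 = 0.60 | 10/10 = 1.0 |
| 1.2 | 7.2/12 = 0.60 | 12/10 = 1.2 |
| 1.5 | 9/15 = 0.60 | 15/10 = 1.5 |

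With A = C = 10 the side ratio is 1.00 for every k.

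**4. What if the two sides respond differently?** Then the ratio moves, but it does not identify the size of the effect. With kA = 1.2 and kC = 1.5 it is 7.2/15 = 0.48. With kA = 0.8 and kC = 1.0 it is 4.8/10 = 0.48. The contralateral threshold rises by 50% in the first case and not at all in the second, yet the index is the same.

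**The case against.** The strongest reply is that the article is a condensed text. It names ice water as the conditioning stimulus, so a conditioned measurement is clearly intended, and it sends the full procedure to Additional file 1. That file may describe before-and-during measurements and testing on both sides. The side ratio, which is also formed for the perception threshold, could be a normalising step and not the final index.

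This stands in part. The file could show that the right data are collected, and nothing here says they are not. But the point is not an omission. The article states one formula under its analysis method for this outcome, and that formula has no conditioning contrast and conflicts with the electrical test site in the same section. If Additional file 1 says otherwise, the two texts still have to be reconciled.

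Three stronger readings are tempting and are not supported:

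- *The index has no sensitivity at all to conditioning.* This holds only if conditioning acts by the same factor on both sides, which the documents do not say. Step 4 of the working shows the ratio moving when the factors differ.
- *The median of three determinations removes the conditioning effect.* That would require conditioned and unconditioned values to be pooled in one median. The text describes repeats of an ascending test, with the median used against outliers, and does not suggest pooling.
- *The numerator is missing for both stimuli.* It is clearly missing for the electrical test. For pressure, the trapezius side is simply not stated.

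**Conclusion.** The point holds, for a secondary outcome. As written, the conditioned pain modulation analysis yields a measure of side asymmetry. It has no contrast between thresholds without and with ice water; an effect common to both sides would cancel, and only a side-differential effect could show. For electrical stimulation, the described test does not supply the affected-side value that the formula needs. Followed literally, the outcome at T0 and T3 would not measure endogenous pain inhibition.

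The reach is limited. This is one of twelve secondary outcomes, and the Statistical methods section treats the secondary analyses as explorative. The primary NRS comparison, the sample size and the non-inferiority conclusion do not depend on it. A reader might infer that the outcome is lost, but that does not follow: if thresholds are recorded in both conditions, a proper index can be derived from them.

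The conclusion rests on the article's text alone, with Additional file 1 unseen. The thresholds in the working are assumed; the cancellation is algebra and does not depend on their values, only on an equal proportional effect on the two sides.

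**What to change.** 1. Define the conditioned pain modulation effect separately for electrical and pressure stimulation, at one and the same site, as the change or ratio of the median pain threshold during or after ice water against the median before it. Take the medians within each condition.
2. Report any affected/contralateral ratio separately, labelled as asymmetry, and only for thresholds measured on both sides.
3. State the side of the trapezius test, and reconcile the sites and the formula in the article with Additional file 1.

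The cost is wording in the protocol and the analysis plan. No new data are needed, provided thresholds are recorded both without and with conditioning. That should be confirmed against Additional file 1 and the case report form.

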In the Netherlands, CRPS patients are treated according to the Dutch guideline for CRPS [12]. This guideline recommends esketamine treatment when the pain is severe (Numerical Rating Scale ≥7) and other more conservative therapies have failed. Both outpatient and inpatient esketamine treatments are offered in the Netherlands [5]. The clinical protocol of our Center for Pain Medicine is a 6-day inpatient admission for continuous esketamine administration, with almost 50% of the patients still reporting pain relief 4 weeks after treatment [13]. Unfortunately, bed shortages and financial boundaries limit inpatient esketamine infusions. In addition, the COVID-19 pandemic showed that hospital bed capacity is limited and esketamine infusions for CRPS have been postponed or cancelled due to the scarcity of hospital beds and health care professionals during the pandemic. Esketamine infusions in an outpatient setting might increase flexibility and availability of esketamine treatment and may reduce costs. However, differences between intermittent and continuous esketamine infusions for CRPS have never been compared in randomized controlled trials (RCTs). To study this, we will conduct a non-inferiority RCT to assess whether a series of intermittent esketamine infusions, in 3 months every 2 weeks a day-care outpatient infusion of 6 hours, is non-inferior to a 6-day inpatient admission with continuous esketamine administration in establishing pain relief in CRPS patients. In addition, in both treatment settings, several objective parameters will be assessed to investigate mechanisms responsible for pain relief. Hopefully, this will lead to the identification of predictors of response to esketamine and in the future CRPS patients will be selected for esketamine treatment in a mechanism-based manner. Furthermore, the results of this study will include a cost-effective analysis. This study will help to guide decisions about the use of esketamine treatment for CRPS patients.

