### Recruitment, allocation and blinding

CRPS patients who are selected for a treatment with intravenous esketamine will be placed on the regular clinical waiting list of the Center for Pain Medicine. Patients will be selected chronologically from this waiting list for esketamine treatment and are contacted by a researcher for trial information. The expected duration of the study inclusion period will be approximately 3 years. The first patients will be included in 2022. Patients can withdraw from the study at any time without giving reasons. This is without any consequences for further medical treatment. Patients who are not willing to participate in this study will receive standard care (inpatient esketamine infusions).

After informed consent, patients will be enrolled and randomized using Castor software (Castor EDC). Previous treatments with esketamine may influence the outcomes of this clinical trial and therefore stratified randomization is performed with randomization blocks according to whether patients received previous esketamine treatment. The randomization will be done with an allocation ratio 1:1. The patients, researchers and statistician will not be blinded during the data collection and analysis. The researcher will enroll patients and will assign patients to the interventions after randomization.

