The strengths of this study design are the randomized design and the stratification of patients based on whether they have had esketamine infusions in the past. Another strength of this study is that several objective parameters for esketamine treatments and the cost-effectiveness are assessed. Complementary to further understandings of esketamine mechanisms, diagnostic tests and biomarkers are needed to predict response on esketamine infusions for CRPS patients [13, 27, 53]. By incorporating a peripheral blood inflammatory parameter, conditioned pain modulation, thermography and QST, our research group hopes to provide information on differences between responders and non-responders to esketamine treatment. This paves the way to a more mechanism-based approach in selecting CRPS patient for esketamine treatment. A potential pitfall of the study protocol is that, although CRPS is a multi-mechanism syndrome, patients receive esketamine as a monotherapy. Targeting only a single mechanism might not be sufficient in CRPS [3]. Furthermore, patients cannot be blinded for an intermittent or continuous esketamine treatment. Of note, although the decisions of our research group on the treatment protocols for esketamine administration have been made after thorough consideration, significant uncertainty exists for the most ideal treatment regimen for esketamine infusions and may also differ for each individual CRPS patient. We acknowledge that all decisions on the length and dose of esketamine administration can influence the outcome parameters in this RCT.

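### Thermography is called objective but falls under a blanket statement that researchers are unblinded; only patient blinding is said to be impossible, and coded reading of stored images is not considered.

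*Protocol article*

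**What the plan says.** Protocol article, Recruitment, allocation and blinding: "The patients, researchers and statistician will not be blinded during the data collection and analysis". No outcome is exempted. The same section adds that "The researcher will enroll patients and will assign patients to the interventions after randomization", so the research team knows the allocation. Table 1 places allocation before the T0 visit, so the arm can be known even when the baseline image is taken.

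Outcomes: "Fourth, temperature asymmetry will be measured by thermographic imaging at T0 and T3". The section on the baseline measurement gives the purpose, namely that "thermography will be conducted to detect temperature differences that may be caused by esketamine treatment", and says who does it: "Specialized researchers use a camera from FLIR Advanced Thermal Solutions to detect temperature asymmetry (FLIR T1020". It does not describe how temperatures are obtained from the image.

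Background promises that "in both treatment settings, several objective parameters will be assessed to investigate mechanisms responsible for pain relief". The Discussion says "Another strength of this study is that several objective parameters for esketamine treatments and the cost-effectiveness are assessed" and, shortly after, names thermography among the measures meant to separate responders from non-responders: "By incorporating a peripheral blood inflammatory parameter, conditioned pain modulation, thermography and QST". The one blinding limitation it gives is that patients cannot be masked to an intermittent or a continuous regimen.

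**The concern.** That patients cannot be masked is no reason for leaving the person who reads an image unmasked. Quantitative sensory testing and conditioned pain modulation need live contact with the patient, so masking the assessor is harder there. A thermal image can in principle be kept and read later by someone who sees neither arm nor visit. The article rules this out through a general statement and gives no reason.

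At stake is the between-arm comparison of temperature asymmetry. If the asymmetry value depends at all on the reader, for example on which area of each limb is sampled, an expectation about one regimen could shift it. An outcome labelled objective would then carry some of the assessor subjectivity that the label suggests is absent.

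**Working it through.** **1. Does the unblinded status cover thermography?** Three statements, side by side:

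| Place in the protocol article | Content |
|---|---|
| Recruitment, allocation and blinding | Researchers unblinded at collection and at analysis, no exception |
| Outcomes | Temperature asymmetry is a secondary outcome at T0 and T3 |
| Baseline measurement T0 | Researchers do the thermography, to look for effects of esketamine |

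Knowledge of the arm by those who measure this outcome follows directly. It is a stated choice, not a detail left to the full protocol.

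**2. Is a reason given?** No. The Discussion's remark on blinding concerns patients only.

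**3. What is not stated?** Whether images are stored, whether regions are fixed or chosen by hand, whether software extracts the temperatures, and whether the reader sees the visit. A route to bias through reader judgement is therefore a possibility and is not documented.

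**4. Size.** The plan gives no SD, expected difference or power for thermography, so there is no figure of its own to reproduce. The only usable inputs are the planned 60 patients and the 1:1 allocation, which give 30 per arm. The rest is assumed.

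Let b be the net between-arm reading shift, in SD units of the quantity compared. The standard error in the same units is √(2/30) = 0.258. With no true difference, the two-sided 5% error rate becomes Φ(−1.96 + b/0.258) + Φ(−1.96 − b/0.258).

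| Assumed b (SD) | b/0.258 | Error rate |
|---|---|---|
| 0 | 0 | 5% |
| 0.1 | 0.39 | about 7% |
| 0.2 | 0.77 | about 12% |
| 0.3 | 1.16 | about 21% |
| 0.5 | 1.94 | about 49% |

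In degrees, with an assumed SD of 0.8 to 1.5 °C, the standard error is 0.8 × 0.258 = 0.21 to 1.5 × 0.258 = 0.39 °C. A net shift of 0.2 °C then gives about 8% to 16%, and 0.3 °C about 12% to 31%. These figures use an SD at a single time point.

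**5. What b means when T0 is taken into account.** For change from baseline, the net shift is (shift in arm A at T3 − shift in arm A at T0) − (shift in arm B at T3 − shift in arm B at T0). A between-arm shift that is equal at both visits cancels. If T3 is instead regressed on T0 with slope β, a shift b present at both visits leaves b(1 − β). Statistical methods specifies linear regression for continuous outcomes but does not say which form applies. The SD of change would also depend on the T0–T3 correlation, which is not given. The tabulated rates are therefore illustrations of sensitivity, not estimates.

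**The case against.** The strongest reply is that the route to bias is not in the text. The article names the camera, its purpose and its operators, and stops there. Region definitions and image handling normally sit in a full protocol or a measurement procedure, neither of which is shown. If software extracts temperatures over fixed regions, there is little left for a reader to influence. This stands. It means that absent region definitions cannot be held against the article, and that bias can only be stated conditionally. It does not remove the point, because the article does fix masking, and fixes it as none.

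Objective can also fairly mean measured by an instrument rather than reported by the patient. Read that way, an unmasked operator does not contradict it, so there is no formal inconsistency. A reader might go further and infer that the Discussion offers these measures as an independent check on open-label pain scores. It does not. It ties them to differences between responders and non-responders and to mechanism-based selection, and for a responder contrast knowledge of the arm is not the direct threat.

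A reader might also infer that the researchers choose regions by hand and know whether an image is from T0 or T3. Knowledge of the visit is plausible from the blanket statement, but neither is stated. Both arms receive the same drug, and nothing in the documents suggests the direction in which a reader would lean.

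Finally, coded reading has limits. The staff who took an image may recognise it, and bias at acquisition is untouched. Both reservations stand.

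**Conclusion.** The point holds as a cheap improvement. The article leaves researchers unblinded for an outcome that it counts among its objective measures, and gives no reason that applies to reading images. Whether this biases anything depends on whether temperature extraction involves judgement, which the article does not say. The documents do not allow the size to be quantified; the error rates in the working rest on assumed SDs and shifts, and a shift equal at both visits would cancel in the change.

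The consequence is small. Thermography is one of many secondary outcomes, which Statistical methods describes as exploratory and analyses without multiplicity correction. The primary NRS comparison, the sample size and the non-inferiority conclusion are unaffected. The point gives no ground for changing the statistician's blinding status.

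**What to change.** - In Recruitment, allocation and blinding, add an exception for the reading of thermographic images. Leave the rest of the statement, including the part on the statistician, as it is.
- In Baseline measurement T0, say how temperatures are extracted. State that stored images carry a random code with arm and visit removed, that the existing researchers extract temperatures over prespecified regions from the coded images in batches, and that the key is released only after extraction. If the full protocol already defines the regions, refer to it.
- If this is not feasible, list unmasked reading as a limitation in the Discussion, beside the one on patients.

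Cost: file coding, batch reading by the same staff, and no image result available at the visit. The documents give no cost figure, and they do not say that images are stored; both are assumed to be manageable. Bias at image acquisition is not removed.
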